## Abstract

**Background:**

Preterm birth (PTB) is a leading cause of neonatal morbidity and mortality. More than 13 million babies are affected globally every year and PTB will contribute to over 900,000 deaths. In the UK, PTB affects 8% of pregnancies and costs more than £260 million annually in neonatal care. Identifying those at risk of this devastating complication of pregnancy and implementing preventative treatment remains a maternal health priority. The mainstay of PTB prevention has been assessment of cervical length (CL) in women at high-risk of PTB. However, CL has limitations, namely it is invasive, user dependent and varies over time through pregnancy. Importantly, not all those who are high-risk with a short CL will subsequently deliver preterm and CL screening doesn’t identify a sub-set of women who have a spontaneous PTB without a short cervix. Therefore, existing care pathways for managing PTB can potentially benefit from additional assessments of risk. Novel ways of assessing cervical structure and function may improve our ability to predict spontaneous PTB and refine preventative intervention. This feasibility study will explore the use of a new antenatal test of cervical stiffness for assessing risk of spontaneous PTB in a high-risk singleton population.

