**Methods:**

PRECISION is a single site prospective, feasibility, cohort study of asymptomatic women with singleton pregnancies at high risk for spontaneous PTB attending an inner-city tertiary maternity hospital in the UK. All study participants will be undergoing routine screening and management of PTB as per local guidance (NICE/Saving Babies Lives guidance) including CL screening with transvaginal ultrasound. Cervical stiffness will be assessed using the Pregnolia System; a novel, licensed, CE-marked, aspiration-based device. A measurement is obtained by applying the device directly to the anterior lip of the cervix, visualised via placement of a speculum, and gives a quantitative assessment of cervical stiffness represented as the Cervical Stiffness Index (CSI, in mbar). Participants will undergo cervical stiffness assessments at up to three timepoints in the second trimester between 14^+0^ weeks and 25^+6^ weeks gestation. The cervical stiffness index data will be paired with routine PTB clinic CL measurements taken at the same time points. The primary outcome will focus on the feasibility of using this novel antenatal test in this high-risk population and explore any association between cervical stiffness and PTB.

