**Fig 1 pone.0316297.g001:**
[figure not shown]
Study Flow Chart.

Participants will complete a structured questionnaire after their first clinical examination in the study. This questionnaire will collect patient experience of the cervical stiffness assessment in comparison to standard CL assessment and collate data as to the acceptability of the assessment in this patient population (supporting information S1 Fig). Participants attending at Study Visit A time point will be invited to consent to gifting two high vaginal swabs as samples for future vaginal-microbiome research. These gifted samples will be obtained during the speculum procedure used for cervical stiffness assessment.

All study participation will coincide with the participants routine PTBC appointments, and participants will continue to receive all PTB intervention and surveillance as guided by their clinicians and as per national and regional PTB guidance (SBLCBV3, NICE Preterm Labour and Birth guidelines and the North West Regional network PTB guideline) [1,3,26]. Study procedures at each visit are detailed and explained in the study flow chart (Fig 1).

In this feasibility study we will recruit patients for 15 months and expect to achieve a cohort of 60 patients based upon expected high-risk clinic referrals and an assumed recruitment rate of 40%.

Participants will remain in the study following recruitment until delivery and discharge from hospital. Study outcomes will be collected from electronic hospital records for the participant and their baby.

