## Study objective

The PRECISION study has the following objectives

To obtain cervical stiffness measurements during the second trimester in high-risk singleton participants to:Determine the reliability and best interpretation of triplicate measurements in this patient group at this gestation.Explore any potential association between second trimester cervical stiffness and gestation at delivery.Compare cervical stiffness assessments to CL measurements taken concurrently and explore the association with gestation at delivery.•To explore the acceptability of this assessment tool in this patient population for PTBC screening.•Upon positive conclusion of the PRECISION feasibility study, to inform for the design of an appropriately powered study to assess the capability of this novel device for PTB prediction.

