### Study outcome

The Pregnolia System is a novel device with no published data providing cervical stiffness index results in asymptomatic women who are high-risk for PTB. This will be the first study to provide this data and will guide how further research using this novel assessment tool can be most appropriately designed.

Previous studies at this study site over the last 10 years have achieved acceptable recruitment when obtaining blood samples and have demonstrated a notable PTB rate in a similar asymptomatic high-risk population (18%) [29,30]. However neither can be extrapolated to the PRECISION study due to the difference in study procedures and change in clinical practice over this time following the introduction of the Saving Babies Lives Care Bundle V3 [3]. Subsequently, this feasibility study will provide an accurate recruitment rate demonstrating this population’s acceptability for this unique assessment in clinical practice. This study will provide an updated outcome incidence of PTB in this appropriately phenotyped study population and an estimate of the variance for cervical stiffness using the Pregnolia System. Together this data will infer the design of a larger study to establish a predictive model for spontaneous preterm birth (<34 weeks) in this patient population [31–33].

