### Statistical analysis

Descriptive statistics will be generated and presented as means (SD), median (IQR) and frequency of observations (percentages) with 95% confidence intervals as appropriate.

Cronbach’s Alpha will be used to assess the reliability of the device to produce consistent readings at different time points. It compares shared variability among the measurements with the overall variance. If the device is reliable then there should be high covariance amongst the measurements relative to the variance. Cronbach’s alpha alongside descriptive statistics with 95% confidence intervals will inform best use of the triplicate CSI measurements taken at each study visit. Specifically exploring whether the first, average, median or lowest measurement of the three readings should be utilised in further analysis and most importantly inform best use of the CSI results in clinical practice.

An estimate of the variability in the outcome measure will be calculated and then applied to a sample size calculation for a further definitive study.

Diagnostic performance of cervical stiffness assessments using the Pregnolia System for PTB will be demonstrated through receiver operating characteristic curves with area under the curve and 95% confidence intervals being calculated, as well as aiming to define the optimum cut-off value for predicting PTB. Cervical length diagnostic performance data will also be generated for direct comparison.

Any association between cervical stiffness and gestational age at delivery will be explored using scatter plots and linear regression. Longitudinal data will be explored using time series plots, and box plots with a sensitivity analysis completed on all participants with a complete data set.

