## Discussion

The PRECISION study aims to evaluate the use of cervical stiffness as a novel assessment tool for PTB risk prediction in high-risk asymptomatic singleton pregnancies. Identification of a new effective screening tool that can either work independently or alongside current screening tools may hold significant potential to improve PTB management. Improved identification of those at risk could allow for earlier PTB interventions and effective PTB optimisation bundles to be appropriately implemented.

To date there have been no clinical studies of the Pregnolia System performed in a high-risk pregnancy population for the prediction of spontaneous PTB. With the resource constraints of research, not all interventions can be tested for both efficacy and effectiveness. Feasibility studies are recommended to establish which tools should be recommended for efficacy testing [24]. Although other research studies are currently underway to attempt to assess this tool [36], we have designed a feasibility study to firstly assess recruitment rates, acceptability in practice and identify the likelihood of clinical effectiveness prior to designing and costing an appropriately powered study to attempt to demonstrate efficacy of this tool. We also wish to inform our analysis on how best to use the triplicate readings recommended by Pregnolia in preparation for an appropriately designed larger study in our population that can then fully explore the device’s potential predictive capacity for PTB.

Although this feasibility study is limited by its single centre design, its strengthened by its’ setting in an inner-city tertiary maternity hospital that serves a diverse population with a known high PTB rate. The pragmatic study design allows all eligible participants who attend the PTB service at the study site to participate and captures use of the assessment tool in real clinical practice. The clearly defined study population will allow the results from this feasibility study to be truly applicable to the population a future clinical prediction model would serve.

The PRECISION study will provide unique data of cervical stiffness in high-risk asymptomatic singleton pregnancies that is not yet available in the literature. This novel clinical data will be instrumental to inform a larger study that has the potential to implement important change in such a high-risk cohort of obstetrics.

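### As written, the analyses treat cervical stiffness and cervical length separately and do not show whether stiffness adds to length; one exploratory joint regression on the paired data would

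*Protocol article*

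**What the plan says.** The Statistical analysis section of the protocol article plans three things that bear on this point.

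- ROC curves with AUC and 95% confidence intervals for CSI, and a search for the best cut-off.
- The same kind of result for CL: "Cervical length diagnostic performance data will also be generated for direct comparison".
- For the continuous outcome: "Any association between cervical stiffness and gestational age at delivery will be explored using scatter plots and linear regression". CL is not named here.

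The Study objective section includes: "Compare cervical stiffness assessments to CL measurements taken concurrently and explore the association with gestation at delivery". The abstract's Methods add: "The cervical stiffness index data will be paired with routine PTB clinic CL measurements taken at the same time points".

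On the intended role of the test, the abstract's Background says that "existing care pathways for managing PTB can potentially benefit from additional assessments of risk", and the Discussion speaks of a tool that "can either work independently or alongside current screening tools". The Study outcome section leaves the predictive model itself to a larger study, which this one is meant to inform.

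**The concern.** Every woman in this clinic already has CL scans, so the practical question for a new cervical test is what it tells the clinic once CL is known. Two AUCs side by side do not answer that, and neither does a regression that contains CSI alone.

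The error can go either way. CSI may look predictive only because it is correlated with CL, and a larger study would then be built around a marker with nothing to add. Or CSI may look weaker than CL and be dropped although it carries independent information. Since the study exists to inform the design of a larger one, a first estimate of the CSI association given CL is worth having. The stated analyses do not produce it.

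**Working it through.** **Plan's own figure.** In the Study design section the investigators "expect to achieve a cohort of 60 patients based upon expected high-risk clinic referrals and an assumed recruitment rate of 40" per cent. The number of referrals is not given, so the figure can only be solved backwards: 60 / 0.40 = 150 eligible women, or 150 / 15 = 10 per month over the 15 months. It is a recruitment forecast, not a power calculation.

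**Inputs.** From the article: n = 60; withdrawals kept below 20%, so 0.80 × 60 = 48 as a lower case; a historical preterm birth rate of 18%, which the article says cannot be carried over to this study. Assumed, because the article gives no values: two-sided alpha 0.05; CSI-CL correlation ρ = 0.5 (range 0.3 to 0.7); CL separating cases from non-cases by one standard deviation.

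**1. How a pure proxy would look.** With CL normal in each group and one SD apart, AUC(CL) = Φ(1/√2) = 0.76. If CSI relates to outcome only through CL, AUC(CSI) = Φ(ρ/√2):

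| ρ | AUC of CSI alone | Added value given CL |
|---|---|---|
| 0.3 | 0.58 | none |
| 0.5 | 0.64 | none |
| 0.7 | 0.69 | none |

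This is an illustration only. Neither the 0.76 nor the correlations come from the article.

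**2. Why the linear regression is the place for a joint model.** At 18%, the binary outcome would give 0.18 × 60 = 10.8 events, or 10.8 / 2 = 5.4 per predictor with two markers. With 48 women it is 8.6 events and 4.3 per predictor. That is too few for a stable joint logistic model. A linear regression of gestational age at delivery draws on all women with a reading at that visit and an outcome, not only on the cases.

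**3. Cost of adding CL.** The smallest correlation detectable with 80% power is tanh[(1.960 + 0.842)/√(n − 3 − k)], where k is the number of adjusting variables. At n = 60 this is 0.355 for CSI alone (k = 0) and 0.358 with CL (k = 1). With CL and gestation at measurement (k = 2) it is tanh(2.802/√55) = 0.361. Residual degrees of freedom for that last model are 60 − 4 = 56.

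Collinearity multiplies the standard error of the CSI slope by 1/√(1 − ρ²): 1.05, 1.15 and 1.40 for ρ = 0.3, 0.5 and 0.7. This is before any reduction in residual variance from including CL.

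**4. Power for the CSI term**, with k = 2: Φ[atanh(r)·√(n − 5) − 1.960].

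| Partial r | n = 60 | n = 48 |
|---|---|---|
| 0.20 | 32% | 26% |
| 0.30 | 63% | 53% |

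At n = 60, power is 77% for r = 0.35 and 88% for r = 0.40. For r = 0.30 at n = 60, for example, atanh(0.30) = 0.3095; 0.3095 × √55 = 2.295; Φ(2.295 − 1.960) = 0.63. An observed partial correlation of 0.30 with 60 women would have a 95% interval of tanh(0.3095 ± 1.960/√55) = 0.05 to 0.52.

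**The case against.** **The text does not exclude a joint model.** It names CSI in the regression but does not say that CL is left out, and covariates in an exploratory regression are often left to a fuller document. This stands in part: a reader might infer that the study cannot show added value, and that goes too far, because the paired data would allow the analysis. What remains is that the article names one measure for the regression, assigns the other to a separate comparison, and nowhere describes a model with both.

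**Added value is not a listed objective.** A reader might infer that the plan contradicts its own aims. The documents do not support that. The objectives ask for a comparison with concurrent CL and for association with gestation at delivery, and prediction is left to the larger study. The interest in added value follows from the rationale and Discussion, so this is an improvement and not a contradiction.

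**Per-visit numbers may be smaller.** It would be wrong to assume that the regression uses all 60 women at each visit. Assessments number up to three, recruitment runs to 25+6 weeks so that late entrants miss earlier visits, and withdrawals occur. With an assumed 40 women, power at a partial correlation of 0.30 is Φ(0.3095 × √35 − 1.960) = 45%.

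**CL guides care.** According to the two assessment sections, CL is known to participant and clinician and informs intervention, while CSI is blinded at the visit. Treatment prompted by a short cervix can weaken the link between CL and outcome and distort what CSI appears to add. This stands and must be stated with the result. The CSI-only regression is exposed too wherever CSI and CL are correlated.

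**A slope is not prediction.** A coefficient for gestational age across all births is not added prediction of birth before 34 weeks, the primary clinical outcome, and the article does not say how iatrogenic births enter this regression. Both points hold, and the second affects the CSI-only model equally.

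**The AUC illustration is hypothetical.** With 11 events among 60 women, an AUC of 0.64 would have a Hanley-McNeil 95% interval of roughly 0.45 to 0.83. It shows a mechanism, not a forecast, and such a result would not by itself decide on a larger study.

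**Conclusion.** The point holds in limited form. As written, the Statistical analysis section does not show whether stiffness carries information beyond length, although the measures are paired, their comparison is an objective, and the test is presented as a possible addition to CL. Adding CL to the planned regression is feasible: the smallest detectable correlation at n = 60 hardly moves, and the main price is collinearity, whose size depends on an assumed CSI-CL correlation.

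The joint model would estimate moderate associations imprecisely and would probably miss small ones. It can generate a hypothesis for the larger study but cannot settle added value, and CL-guided care limits its interpretation further. The point is minor: a cheap improvement that leaves the feasibility aims untouched.

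**What to change.** In the Statistical analysis section, after the sentence on linear regression, add an exploratory analysis. For each study visit, fit gestational age at delivery on CSI and CL together, with exact gestation at measurement as a covariate, since each visit window spans four weeks. Fit the model with and without CL on the same women. Report the CSI coefficient with its 95% confidence interval from both fits, and the number of women contributing.

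Label the result exploratory and hypothesis-generating for the larger study, and state three cautions with it: the wider CSI interval, the limited power at per-visit sample sizes, and the possible distortion because CL is unblinded and guides care while CSI is blinded.

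The cost is one further regression per visit on data already being collected. No new measurements, visits or participants are needed.

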## Data management plan

All study participants are allocated a unique participant identification number and all data relating to that patient is pseudonymised. Study data is initially captured using a paper CRF. The data from the paper CRFs are then transcribed to an electronic CRF within a bespoke, password protected, study database (REDCAP). The Chief Investigator (CI) will preserve the confidentiality of participants taking part in the study and will abide by the EU General Data Protection Regulation 2016 and Data Protection Act 2018.

### Consent and criteria for withdrawal

Consent to enter the study must be sought from each participant only after a full explanation has been given, an information leaflet offered, and time allowed for consideration. Signed participant consent will be obtained. The participant can decline to participate without giving reasons and this will not impact upon further care. All participants are free to withdraw at any time from the study without giving reasons and without prejudicing further care.

In addition, the CI may decide, for reasons of medical prudence, to withdraw a participant. In either event, the Sponsor will be notified and the date and reason(s) for the withdrawal will be documented in the participant source data. If a participant withdraws or is withdrawn, ideally, they should remain in the study for the collection of outcome data. If the participant states their wish not to contribute further data to the study, collected data will be removed from the study database and no further outcome data will be collected.

## Monitoring and safety

A Study Management Group (SMG) comprising the CI, principal investigator, co-applicants, and core study management staff meet at regular intervals throughout the course of the study and holds responsibility for the day-to-day running and management of the study. The need to stop the study will be determined by the SMG and the decision will be based upon data integrity and participant safety.

All adverse events for this study are recorded at each study visit on the study CRF. This is a non-interventional study we therefore do not anticipate many serious adverse events. The Pregnolia System is a licensed, CE-marked, non-invasive medical device and the risk of adverse events related to the measurement is small. The device has a very good safety profile, and the manufacturer has not received any serious adverse event reporting related to the medical device either in studies or clinical practice at the time of starting the PRECISION study.

### Ethical considerations and declarations

The Wales Research Ethics Committee 3 has given approval for this research (23/WA/0044). All patients will be given written informed consent prior to entry to the study and will be aware that participation is completely voluntary.

### Status and timeline of the study

PRECISION has been open for recruitment since 6^th^ July 2023. Recruitment is due to finish in October 2024, and patient follow up complete in January 2025. The study will end at 20 months from opening which includes all recruitment, follow up and analysis of data.

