### Cervical length assessment

Clinical staff will perform transvaginal ultrasound assessment of CL using a GE Voluson E10 ultrasound machine and 7.5MHz transvaginal probe. All measurements will be performed with the woman in a supine position with an empty bladder in the sagittal plane measuring from the internal to external cervical OS. The full length of the cervical canal will be visualized with the closed portion of cervix remaining being measured in triplicate.

The shortest CL measurement of the three readings will be documented as the final CL measurement for that study visit. CL measurements will be known to both the participant and clinician at the time of assessment and will be used to guide ongoing surveillance and PTB intervention as per the clinical team decision-making and regional guidelines.

The study procedure order is further outlined in the study flow chart (Fig 1) and schedule of study procedures (Table 1). Participants will remain in the study for a maximum of 31 weeks, from initial visit to PTBC until point of discharge after delivery, or infant aged 1 month. Assessments will take place at specified timepoints as shown in the study schedule (Table 1).

**Table 1 pone.0316297.t001:** Schedule of Study Procedures.

Order of Procedures	At PTBC triage (12 weeks)	Study Visit A (14+0−17 + 6 weeks)	Study Visit B (18 + 0−21 + 6 weeks)	Study Visit C (22 + 0−25 + 6 weeks)	Postnatal & End of study
*Patient Eligibility*	**X**				
*Patient information Leaflet provided*	**X**				
*Informed Consent*		**X**			
*Pre-Sample Collection Questionnaire*		**X**			
*High Vaginal Swab Collection (2 gifted samples)* * *optional*		**X**			
*Cervical Stiffness Measurement*		**X**	**X**	**X**	
*Cervical Length Scan*		**X**	**X**	**X**	
*Post-Assessment Patient Questionnaire*		**X**			
*Delivery Outcomes*					**X**
*Maternal Postnatal Outcomes*					**X**
*Neonatal Postnatal Outcomes*					**X**
*Adverse Event Reporting*		**X**	**X**	**X**	**X**

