### Feasibility outcomes

Our feasibility outcomes of interest relate to whether the study procedure is acceptable, participant adherence and retention to the study is achieved, data collection is feasible, and that cervical stiffness assessment fidelity is maintained with adequate reliability and safety[34].

Our feasibility outcomes will be defined as follows;

1)Participant acceptability of cervical stiffness assessment in PTB clinica.Qualitative questionnaire following assessmentb.Number of participant withdrawals throughout the study duration (aim for < 20%)c.Reasons for non-participation collected of eligible women approached for the study2)Adherence to the protocola.Measured as number of protocol deviations3)Adherence to data collectiona.Numbers of missing data (aim for < 10%).b.Loss to short term follow up (aim for < 5%)4)Safety outcomesa.Incidence of adverse events5)Cervical stiffness fidelitya.Ability to obtain triplicate cervical stiffness measurements (aim for > 90%)b.Triplicate measurement reliability (aim for > 0.8 Cronbach’s Alpha)6)Inputs for sample size and power calculation of future studya.Determine sPTB rate in the total study population (participating and non-participating PTBC patients) to inform current sPTB rate post national guidance care implementationb.Determine estimate of CSI variance using the Pregnolia Systemc.Determine recruitment rate to the study to inform sample size required

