### Study endpoint

The study will end when the last recruited woman has delivered and both herself and her baby have been discharged from hospital, or 1 month after delivery, whichever is sooner and all planned analysis of collected data has taken place.

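### The calendar (follow-up complete in January 2025, study end at 20 months) is too short for the until-delivery, up-to-31-week follow-up that the protocol sets elsewhere

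*Protocol article*

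**What the plan says.** The protocol article describes the length of follow-up in four places.

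- **Status and timeline of the study:** The opening date is given first: "PRECISION has been open for recruitment since 6^th^ July 2023". For the later milestones the section says: "Recruitment is due to finish in October 2024, and patient follow up complete in January 2025". Closure is set at 20 months after opening, a period that has to hold recruitment, follow-up and analysis.
- **Study design (text below Fig 1):** The recruitment plan reads: "In this feasibility study we will recruit patients for 15 months and expect to achieve a cohort of 60 patients". On the length of participation it says: "Participants will remain in the study following recruitment until delivery and discharge from hospital". No calendar or postnatal limit is given here.
- **Cervical length assessment (closing paragraph, before Table 1):** "Participants will remain in the study for a maximum of 31 weeks, from initial visit to PTBC until point of discharge after delivery". An infant age of one month is named as the alternative stopping point.
- **Study endpoint:** "The study will end when the last recruited woman has delivered and both herself and her baby have been discharged from hospital". A cap is then attached in the same sentence: "or 1 month after delivery, whichever is sooner". Completion of the planned analysis is a further condition.

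On entry gestation, Study design allows recruitment from 14+0 to 25+6 weeks, while Table 1 marks informed consent only at Visit A (14+0 to 17+6). The primary clinical outcome is PTB before 34+0 weeks (Clinical outcomes).

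**The concern.** The first of these places fixes dates; the other three are driven by delivery. If recruitment runs into October, follow-up that closes in January leaves at most about four months, whereas a woman entering in the early second trimester needs about six months to reach her due date.

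The gap matters because any resulting loss would depend on the outcome. Among late recruits, a woman who delivers early is observed before the cut-off and a woman heading for term is not. The analyses most exposed are the regression and scatter plots of cervical stiffness against gestational age at delivery, and any PTB proportion whose denominator is restricted to women who have delivered.

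**Working it through.** **Inputs from the protocol article.** Opening 6 July 2023; recruitment 15 months; expected cohort 60; entry from 14+0; maximum time in study 31 weeks (217 days); follow-up end January 2025; study end 20 months.

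**Reproducing the stated figures**
- Recruitment end: 6 July 2023 + 15 months = 6 October 2024. This agrees with October 2024.
- 31-week maximum: 14+0 to 41+0 is 27 weeks, plus 4 postnatal weeks = 31. This agrees.
- Study end: 6 July 2023 + 20 months = 6 March 2025.
- Follow-up end: 6 October 2024 + 31 weeks = 11 May 2025. This does **not** agree with January 2025. If recruitment runs to 31 October the result is 5 June 2025.

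**The last recruit.** Date of a target gestation = recruitment date + (target gestation − entry gestation). For recruitment on 6 October 2024:

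| Entry | Gestation on 31 Jan 2025 if undelivered | 34+0 | 37+0 | 40+0 |
|---|---|---|---|---|
| 14+0 | 30+5 | 23 Feb | 16 Mar | 6 Apr |
| 17+6 | 34+4 | 27 Jan | 17 Feb | 10 Mar |
| 25+6 | past 40+0 | 2 Dec 2024 | 23 Dec 2024 | 13 Jan |

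January is reached at 40+0 only for entry near 25+6, and the postnatal month then runs to about 12 February. Working backwards with the 31-week maximum, only women recruited by 28 June 2024 are certain to be complete by 31 January 2025, and only those recruited by 1 August 2024 by 6 March 2025.

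**Size if January were enforced as a data cut.** The documents do not give what is needed here, so these are assumptions: uniform recruitment of 60 women, a cut on 31 January 2025, recruitment ending on 6 or 31 October, PTB <34 weeks of 5-18%, PTB <37 weeks of 18-27%, and term births centred at 39.3 weeks. The protocol mentions an earlier 18% PTB rate at the site but says it cannot be carried over to this study.

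Simulation results (women undelivered on 31 January):
- Entry at Visit A: about 5-8 of 60 (8-13%).
- Entry spread over 14+0 to 25+6: about 2-5 of 60 (3-8%).
- Of those undelivered, 91-97% would deliver at term.
- PTB <34 weeks among delivered women: 9.0% becomes 9.4-10.2%; 18% becomes 19-20%.
- With a cut on 6 March instead, about 0.4-4 women are undelivered.

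Hand check for Visit A entry, counting term births only. Mean entry is 111.5 days (midpoint of 98 and 125) and mean term delivery 275 days (39.3 weeks), so a term pregnancy needs 163.5 days after entry.
- Recruitment to 6 October: 117 days to the cut; shortfall 163.5 − 117 = 46.5 days; × 60/458 per day × 0.82 term = 5.0 women.
- Recruitment to 31 October: 92 days to the cut; shortfall 71.5 days; × 60/483 × 0.82 = 7.3 women.

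Adding the few late preterm births gives the simulated 5.2 and 7.8 (PTB <37 weeks of 18%).

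**Primary outcome.** A woman still pregnant at 34+0 is a known negative. With Visit A entry, the average recruitment window leaving a woman short of 34+0 on 31 January is 9.8 days (recruitment to 6 October) or 34.5 days (to 31 October): 9.8 × 60/458 = 1.3 women, and 34.5 × 60/483 = 4.3 before removing those already delivered. So about 1-4 women are undetermined.

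**The case against.** The strongest reply is that nothing has to be lost. The Study endpoint section waits for the last recruited woman to deliver, Study design keeps every participant in until delivery and discharge, and outcomes come from electronic hospital records. No section calls January 2025 a data cut or says that undelivered women are dropped. This stands: the defect is a conflict between the timeline and the other three sections, and outcomes are lost only if the timeline prevails.

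A reader might infer several stronger points that the document does not support:

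- **That the end-of-study rule itself stops before delivery.** It does not. Its weakness is narrower: it is tied to the last woman recruited, who need not be the last to deliver when entry gestation varies by up to 12 weeks.
- **That the PTB rate for sizing the next study is inflated.** Feasibility outcome 6a takes that rate from participating and non-participating clinic patients together. The effect of the calendar on that wider group was not calculated.
- **That the target of under 5% loss to short-term follow-up is breached.** A woman still pregnant and under care is not clearly lost, and whether 5% is passed depends on entry gestation (8-13% against 3-8%).
- **That the one-month limit damages a main outcome.** A baby born at 24-34 weeks is about 28-38 weeks postmenstrual age at one month and may still be an inpatient, but neonatal outcomes are descriptive only. What remains is inconsistent wording between sections.

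The remaining defence, that late recruits enter near 25+6, does not rescue the dates. Table 1 places consent at Visit A, and even entry at 25+6 on 6 October leaves no postnatal month by 31 January.

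**Conclusion.** The point holds as an internal contradiction. On the protocol's own figures, follow-up of the last recruit can run to 11 May 2025 (5 June if recruitment ends on 31 October), after both January 2025 and the 20-month end. This part is date arithmetic and needs no assumption beyond the October end of recruitment.

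The consequence is conditional and moderate. If January were enforced, roughly 2-8 of 60 women would have no delivery outcome, depending on entry gestation and the last recruitment date, and most would be future term births. The gestation-at-delivery analysis would be affected most. A PTB proportion among delivered women would rise by about 1-2 points, which is small against the sampling error of 60 women: for 18%, 1.96 × √(0.18 × 0.82 / 60) ≈ 10 points either way. The primary <34-week status would be open for only about 1-4 women. These sizes rest on the assumed recruitment pattern and delivery distributions. It should be fixed, but it does not undermine the feasibility study.

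**What to change.** 1. Set last follow-up and data lock at the last recruitment date plus 31 weeks (11 May 2025 for 6 October 2024; 5 June 2025 for 31 October), and move the 20-month study end to follow it with time for analysis.
2. If the end date cannot move, either close recruitment earlier (31 weeks before the cut) or treat undelivered women as censored at their gestation on the cut date, counting them as negative for PTB <34 weeks once past 34+0. Do not drop them.
3. Tie the Study endpoint rule to the last participant to deliver, not the last recruited.
4. Reconcile the postnatal limit across Study design (discharge), Cervical length assessment (discharge or one month) and Study endpoint (whichever is sooner), so that one rule applies to mother and baby.

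Cost: follow-up ends 66 to 91 days, about 2-3 months, after the stated 20-month end, plus analysis time. It is record-based, so it needs no extra participants or visits.
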